### Intervention

Subjects will receive regular rehabilitation, including physiotherapy, occupational therapy, and speech and language therapy. Brain areas will be localized using the LOCALITE TMS Navigator system, which will rely on the patient’s magnetic resonance structural images to localize the M1 and V1 [44]. Patients will receive ccPAS treatment with a MagTD magnetic field stimulator from Wuhan Iredell Medical Equipment New Technology Co.

### ccPAS low frequency group

The affected side of the brain will receive dual-target transcranial magnetic stimulation with V1 and M1 as the target sites. The first coil will be placed above V1, tangent to the scalp, at a 45-degree angle to the midline; the second coil will be placed at M1, tangent to the scalp, also at a 45-degree angle to the midline. The stimulation of V1 will occur 18ms before that of M1 [45–47]. The daily ccPAS treatment protocol will consist of 180 pairs of transcranial magnetic stimulation pulses at a frequency of 0.2 Hz for 15 min [48]. The patients will receive the treatment while comfortably seated with relaxed extremities. The stimulation intensity will be set at 120% AMT, which is the minimum machine output intensity that elicits five MEP (motor evoked potential) amplitudes above 100 microvolts during mild contraction of the target muscle for 10 stimulations [49, 50]. MEP was recorded by stimulating M1 to induce contraction of the first dorsal interosseous(FDI) muscle.

### ccPAS high frequency group

The daily ccPAS treatment will consist of 180 pairs of transcranial magnetic stimulation pulses at a frequency of 5 Hz, separated into five segments of 30 pairs of pulses each, with 30 s intervals between segments (3.6 min in total) [30, 51]. Other settings will be the same as the ccPAS Low frequency group.

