## Methods and analysis

### Study design

This study is a double-blind randomized controlled trial, and the protocol is registered with the Chinese Clinical Trials Registry. A total of 69 participants will be divided 1:1:1 into three groups. The control group will receive conventional treatment plus sham ccPAS, the ccPAS low-frequency group received conventional treatment plus 0.2 HZ of ccPAS, and the ccPAS high-frequency group will receive conventional treatment plus 5 HZ of ccPAS.

Each group will receive the intervention five times per week for two weeks. The researcher will follow up with subjects in week six and week fourteen respectively (as shown in Fig. 1 and Table 1).T The primary outcome measure will be the ‘Fugl-Meyer Assessment of the Upper Extremity (FMA-UE)’, secondary outcomes will include ‘The line bisection test’, ‘Modified Taylor Complex Figure (MTCF)’, ‘NIH stroke scale (NIHSS)’, and’ functional Magnetic Resonance Imaging(fMRI)’ as well as ‘Diffusion tensor imaging (DTI)’.

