### Blinding

Each participant will sign a written confidentiality agreement to ensure that information is not shared with others. Randomization of patients will be done remotely by a person who will not be involved in the rest of the trial process. Patients who meet the inclusion criteria will undergo a first basic assessment by a person dedicated to the assessment after signing the informed consent form.

Routine rehabilitation will be done by a physical therapist, an occupational therapist, and a speech therapist in the rehabilitation medicine department. ccPAS treatment will be done by a dedicated researcher, following the given parameters.

The two-week post-intervention assessment will be completed by a second assessor. Follow-up will be done by a third assessor. The data from all assessments will be analyzed by a dedicated data analyst, who will only be provided with the data results for each group without knowing the specific group allocation.

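### High-frequency ccPAS dose does not add up: five segments of 30 pairs deliver 150 pairs, not the stated 180, and do not take 3.6 min; six segments were probably meant

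*Protocol article*

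**What the plan says.** The regimen for the high-frequency arm is given in one sentence of the protocol article, under ccPAS high frequency group. The dose is "180 pairs of transcranial magnetic stimulation pulses at a frequency of 5 Hz, separated into five segments of 30 pairs of pulses each", and the sentence continues "with 30 s intervals between segments (3.6 min in total". The section then carries all remaining settings over from the low-frequency arm.

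The low-frequency arm (ccPAS low frequency group) receives "180 pairs of transcranial magnetic stimulation pulses at a frequency of 0.2 Hz for 15 min". The sham arm copies the low-frequency parameters.

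On delivery, the Blinding section states that "ccPAS treatment will be done by a dedicated researcher, following the given parameters". The Study design section fixes the number of sessions: "Each group will receive the intervention five times per week for two weeks".

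**The concern.** The sentence gives five linked figures: total pairs, frequency, number of segments with their size, rest length and total time. They cannot all be true. The segment count disagrees with the pair total, and it also disagrees with the duration.

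This is the dosing instruction for an experimental arm, and the operator is told to work to the written parameters. Someone who programmes the stimulator from the total delivers 180 pairs. Someone who programmes it from the segment structure delivers fewer. In the second case the high- and low-frequency arms would differ in the number of paired pulses, the one quantity of dose that the text appears to match, and a difference between them could not be put down to frequency at equal pair number. Anyone trying to replicate the regimen meets the same ambiguity.

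**Working it through.** **Inputs, all from the protocol article**

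- High-frequency arm: 180 pairs per day, 5 Hz, five segments of 30 pairs, 30 s rests, 3.6 min = 216 s in total (ccPAS high frequency group).
- Low-frequency arm: 180 pairs, 0.2 Hz, 15 min (ccPAS low frequency group).
- Sessions: 5 per week × 2 weeks = 10 (Study design).

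**Formulas**

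- Pairs = segments × pairs per segment.
- Duration = pairs / frequency + 30 s × number of rests.
- Rests are counted in two ways: only between segments (segments − 1), or after every segment (segments).

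**Step 1: the low-frequency arm as a control.** 180 / 0.2 = 900 s = 15 min. The stated figure is reproduced exactly.

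**Step 2: the high-frequency arm as written.** One segment lasts 30 / 5 = 6 s.

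- Pairs: 5 × 30 = 150, against 180 stated.
- Duration, rests between segments: 5 × 6 + 4 × 30 = 150 s = 2.5 min.
- Duration, rest after every segment: 5 × (6 + 30) = 180 s = 3.0 min.

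Neither 180 pairs nor 3.6 min is reproduced.

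**Step 3: which single change restores agreement?**

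| Segments × pairs | Total pairs | Rests between only | Rest after each |
|---|---|---|---|
| 5 × 30 (as written) | 150 | 2.5 min | 3.0 min |
| 5 × 36 | 180 | 2.6 min | 3.1 min |
| 6 × 30 | 180 | 3.1 min | **3.6 min** |
| 7 × 30 | 210 | 3.7 min | 4.2 min |

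- For 5 × 36: a segment lasts 36 / 5 = 7.2 s; 5 × 7.2 + 4 × 30 = 156 s, or 5 × (7.2 + 30) = 186 s.
- For 6 × 30: 6 × 6 + 5 × 30 = 186 s, or 6 × (6 + 30) = 216 s.
- For 7 × 30: 7 × 6 + 6 × 30 = 222 s, or 7 × (6 + 30) = 252 s.

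With the 30 s rest kept, and among layouts of four to eight segments of 30 or 36 pairs, only six segments of 30 pairs with a rest after each match both 180 pairs and 3.6 min. Keeping five segments would mean changing two other figures: 36 pairs per segment, and a rest of (216 − 36) / 4 = 45 s between segments or (216 − 36) / 5 = 36 s after each.

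**Step 4: size of the discrepancy if followed literally.**

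- Per session: 180 − 150 = 30 pairs; 30 / 180 = 16.7%.
- Over ten sessions: 1,500 against 1,800 pairs.

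**The case against.** The arithmetic is not open to dispute, and the count is spelled out in running prose, so it is not a reading error. The case on the other side is about weight.

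- **The intended dose is easy to see.** The sentence leads with the total of 180, the low-frequency arm has the same total, and other settings are shared. An operator would very likely deliver 180 pairs, and nothing in the article shows otherwise. This stands, and it is why the dose shortfall is stated only as a conditional.
- **The one-word change does not fully repair the sentence.** The article places the rests between segments, and counted that way six segments take 3.1 min. The 3.6 min needs a sixth rest after the last segment. This also stands: the pair total points to six outright, the duration only on that way of counting. It does not help five segments, which fail on either count.
- **The active arms already differ in more than frequency.** Sessions last 15 min in one arm and 3.6 min in the other, and only the high-frequency arm is described with rests. The article does not claim to isolate frequency at equal dose, and the planned one-way ANOVA with pairwise comparisons gives the low-versus-high contrast no special role. A 30-pair gap would therefore add to existing differences. It would still remove the one feature of dose that the text holds equal.
- **Six is an inference.** The article cites sources for the regimen that were not available for this check. Hence the request that the sponsor confirm.

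**Conclusion.** The error is real and the concern holds. The stated segment count contradicts both the pair total and the duration in the same sentence, and nothing elsewhere in the article resolves the conflict. The most likely reading is six segments of 30 pairs, each followed by a 30 s rest.

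The practical effect is nil if six segments are delivered. If five segments of 30 are delivered as written, the high-frequency arm receives 150 pairs per session instead of 180. That conclusion assumes the 5 Hz rate refers to pairs, as the sentence says, and that all ten sessions are given. The sham arm is not affected, because it follows the low-frequency parameters.

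It should be corrected because it is an operational dosing figure. It does not threaten the trial's validity provided 180 pairs are delivered.

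**What to change.** 1. In the section ccPAS high frequency group, change the number of segments from five to six, after the sponsor has confirmed that this was intended.
2. In the same sentence, say whether the rest after the last segment is counted. If it is, 3.6 min is right; if rests fall only between segments, the total should read 3.1 min.
3. Check once that the stimulator programme for this arm delivers 180 pairs per session.
4. Only if 150 pairs are being or have been delivered: state that the two active arms differ in pulse number as well as frequency, and word any conclusion about frequency accordingly.

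The cost is a one-word correction, a short clarification of the time and one equipment check. Sample size, endpoints, randomisation and analysis stay as they are.

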### Control group

The sham stimulation will be achieved by a non-functional sham coil with the same external weight and sound as the real coil, and the rest of the parameters will be performed in the same way as in the ccPAS Low frequency group.

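### The sham coil is described as matched only for weight and sound while inheriting a threshold-based intensity, so patient blinding is at risk, and blinding failure is a dropout criterion

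*Protocol article*

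**What the plan says.** Under Study design, the article states: "This study is a double-blind randomized controlled trial". The Randomization and allocation concealment section withholds the allocation from patients and relatives, from therapists and outcome raters, and from the analysts.

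The Control group section specifies "a non-functional sham coil with the same external weight and sound as the real coil, and the rest of the parameters" handled as in the low-frequency arm. Weight and sound are the only matched features it names.

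The low-frequency section sets those parameters. On intensity: "The stimulation intensity will be set at 120% AMT, which is the minimum machine output intensity that elicits five MEP" responses of the required size in 10 stimulations, during mild contraction of the target muscle. On the method: "MEP was recorded by stimulating M1 to induce contraction of the first dorsal interosseous(FDI) muscle". On the patient's state during sessions: "The patients will receive the treatment while comfortably seated with relaxed extremities".

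The Dropout criteria section lists blinding failure alongside withdrawal, incomplete treatment and access to other treatment.

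**The concern.** A non-functional coil cannot evoke a motor potential. If the sham arm really follows every other low-frequency parameter, its AMT has to be found with a working coil. The same patient would then meet real pulses at threshold testing and none in treatment, from a device for which no matching of scalp sensation is described. That gives the patient a comparison by which sham might be recognised.

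Low frequency against sham is the one active-sham contrast matched in session length and rhythm, so it is where patient blinding should be strongest. FMA-UE is a rated motor performance scale, and all arms receive conventional rehabilitation at the same time. Perceived allocation could affect effort in both.

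The dropout list adds a second problem. If patients who recognise sham are dropped for blinding failure, losses after randomisation depend on the arm, and the groups compared are no longer the groups randomised.

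**Working it through.** **1. Timing of the matched contrast.** Inputs are from the low-frequency section: 180 pairs at 0.2 Hz. 180 / 0.2 = 900 s = 15 min, which reproduces the stated session length. Sham copies this. The high-frequency session is stated as 3.6 min, so it already differs visibly from sham. Timing therefore does not separate sham from low frequency; any recognition would have to come from what the pulses feel like or evoke.

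**2. Exposure.** Five sessions a week for two weeks is 10 sessions; 10 x 180 = 1,800 pairs. A low-frequency patient receives 1,800 active pairs and a sham patient none. This measures the opportunity to notice a difference. It does not measure bias.

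**3. Is sham thresholding implied?**
- The intensity is a multiple of AMT.
- AMT is the "minimum machine output intensity that elicits five MEP (motor evoked potential) amplitudes above 100 microvolts during mild contraction of the target muscle". That requires active pulses over M1.
- The sham arm takes its remaining parameters from this section.
- No sentence says which arms are thresholded or with which coil.

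Two readings remain:
- *Sham patients are thresholded with a working coil.* They have a real pulse to compare with the sham sessions.
- *Sham patients are not thresholded.* They have no such comparison within the trial, but the arms then differ in a pre-treatment procedure, against the wording that the other parameters are the same. Previous experience of TMS, another possible source of comparison, is not among the listed exclusions.

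Under either reading, the sham as described does not by itself support the patient-blinding claim.

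**4. Would a hand response give sham away?** AMT is set during mild contraction, and treatment is given at rest. Muscle state changes between thresholding and treatment in every arm, so a change in hand response is weak evidence of sham. Scalp sensation is the feature left open in the text.

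**5. Reach of the dropout criterion.** Inputs are from Sample size calculation: means 8.11, 6.87 and 17.62, SD 8.83, alpha 0.025, 18 per group, 20% dropout.
- Grand mean: 32.60 / 3 = 10.87.
- Sum of squared deviations: 7.60 + 15.97 + 45.61 = 69.18.
- Noncentrality at n = 18: 18 x 69.18 / 8.83² = 15.97. With 2 and 51 degrees of freedom, power is 0.902, so the stated 18 reproduces.
- Inflation: 18 / (1 - 0.20) = 22.5, rounded up to 23, as stated.
- Allowance: 23 - 18 = 5 patients per arm, to cover all four dropout criteria.
- Six exclusions for blinding failure in the sham arm (6/23 = 26%) would leave 17, even with no other loss.

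The power cost is modest: 17 in every arm gives 0.881. The main issue is comparability, because the exclusions would be concentrated in one arm and selected by what patients perceived.

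**The case against.** The strongest reply is that thresholding of sham patients is nowhere stated. AMT is described under the low-frequency arm, a dummy coil needs no individual threshold, and the Intervention section localises M1 from structural images. Without active thresholding, patients in a parallel-group trial may have no real pulse to compare with. This stands as far as the premise must be called an inference. It does not remove the point, since the sham still has only two matched features named and would then differ in procedure.

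Second, the article does not say that weight and sound are the complete list, and a condensed article commonly leaves coil specifications, patient scripts and guess questionnaires to the full protocol. That stands too: the absence of a questionnaire is not the finding. The finding is that the sham described does not support the label attached to it, and that the plan makes blinding failure a reason to drop a patient.

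Third, a separate researcher delivers the stimulation, and different assessors are used at baseline, after the intervention and at follow-up. A patient's scalp sensation does not in itself unblind a rater. The route to FMA-UE is therefore mainly through patient effort.

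A reader might infer that low frequency against sham is not patient-blind. The documents show a risk, not a failure, and give no guess or sensation data. A reader might also put an expectancy effect in FMA-UE points beside the planning means. The documents give no basis for such a figure, so none is offered.

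**Conclusion.** The point holds as a risk to patient blinding that the described sham does not answer, including for the contrast matched on timing. It should be addressed, with medium confidence.

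It rests on two readings. The first is that the same-parameters wording covers AMT; this is natural but not stated. The second is that a patient dropped for blinding failure leaves the analysis. The article does not say so expressly, but inflating 18 to 23 per arm treats dropouts as lost to the planned number.

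The extent of unblinding cannot be estimated. What can be sized is exposure (1,800 active pairs against none) and the dropout margin (five patients per arm for all causes).

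**What to change.** 1. State how AMT testing is done in the sham arm, including which coil is used, and whether the sham coil reproduces scalp sensation. Reconcile this with the same-parameters wording.
2. Before any threshold testing, give all three arms one standard script: pulses may or may not be felt, whichever arm the patient is in.
3. Ask each patient for an arm guess, with certainty, after the first session and again at the week-2 assessment. Ask the FMA-UE assessor at week 2, after scoring. Report the guesses by arm. Note that the week-2 guess may reflect perceived improvement, so the first-session guess is the cleaner measure.
4. Remove blinding failure as a reason to drop a patient. Keep patients with suspected unblinding in the analysis as randomised.
5. Qualify the double-blind claim for patients by what the guesses show.

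The cost is a script, one question at existing contacts and a few sentences of protocol text, with no new equipment or staff. The downside is that the report may have to concede imperfect patient blinding.

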### Assessment

The patient’s basic information will be obtained from the hospital visit record. The patient’s assessment arrangements are shown in Table 1.

### Fugl-Meyer assessment of the upper extremity (FMA-UE)

The Fugl-Meyer Assessment (FMA) is a widely used method for evaluating sensorimotor impairment in stroke patients and is commonly employed in the clinical assessment of motor function [52]. The Fugl-Meyer Assessment scores have been tested repeatedly and have shown good consistency, responsiveness, and accuracy. The FMA-UE contains 33 assessment items with a total score of 66. The testers can rate the severity of the subject’s motor impairment based on their final score.

### The line bisection test

The patients will be asked to estimate and indicate the midpoint of a horizontal line. It is expected that patients with left neglect will choose a midpoint to the right of true center. Three horizontal, 8-inch black lines, 1-mm thick, will be presented to each patient in a staircase fashion across the page. The extent of each line will be clearly indicated to the patient, who will then be instructed to mark the center.

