**Method:**

This study is a randomized, double-blind controlled clinical trial over a 14-week period. 69 stroke subjects will be enrolled and divided into sham stimulation group, ccPAS low frequency group, and ccPAS high frequency group. All groups will receive conventional rehabilitation. The intervention lasted for two weeks, five times a week. Assessments will be performed before the intervention, at the end of the intervention, and followed up at 6 and 14 weeks. The primary assessment indicator is the ‘Fugl-Meyer Assessment of the Upper Extremity ’, secondary outcomes were ‘The line bisection test’, ‘Modified Taylor Complex Figure’, ‘NIHSS’ and neuroimaging assessments. All adverse events will be recorded.

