**Fig. 1 Fig1:**
[figure not shown]
Flow diagram of study design. ccPAS, Cortical-cortical paired associative stimulation; FMA-UE, Fugl-meyer assessment of upper extremity; MTCF, Modified Taylor Complex Figure; NIHSS, National Institutes of Health Stroke Scale; fMRI, functional Magnetic Resonance Imaging; DTI, Diffusion tensor imaging

**Table 1 Tab1:** Participant timeline

Activity			Study Stuff		Study Period						
				Prestudy	0 week	1 week	2 weeks	2 weeks end	6 weeks end	10 weeks end	
Preparation	Sample size calculation		Investigator A	X							
	Eligibility screen		Investigator B	X		X	X	X	X	X	
	Medical information		Investigator B	X							
	Informed consent		Investigator B	X							
	Random allocation		Investigator B	X							
Intervention	ccPAS Low frequency Group	Conventional therapy	Doctor B + Therapist			X	X				
		0.2 HZ ccPAS	Investigator C			X	X				
	ccPAS High frequency Group	Conventional therapy	Doctor B + Therapist			X	X				
		5 HZ ccPAS	Investigator C			X	X				
	control Group	Conventional therapy	Doctor B + Therapist			X	X				
		sham-ccPAS	Investigator C			X	X				
Assessment	Primary outcome	FMA-UE	Assessor A		X			X	X	X	
	Secondary outcomes	The Line bisection test	Assessor B								
		MTCF	Assessor B		X			X	X	X	
		NIHSS	Assessor B		X			X	X	X	
		fMRI	Imaging doctor		X			X	X	X	
		DTI	Imaging doctor		X			X	X	X	
Statistical analysis			Investigator A					X		X	

ccPAS, Cortical-cortical paired associative stimulation; FMA-UE, Fugl-meyer assessment of upper extremity; MTCF, Modified Taylor Complex Figure; NIHSS, National Institutes of Health Stroke Scale; fMRI, functional Magnetic Resonance Imaging; DTI, Diffusion tensor imaging.

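### Table 1 marks no visit for the line bisection test, a named secondary outcome, and the score has no stated sign convention by lesion side

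*Protocol article*

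**What the plan says.** The Abstract lists the outcomes: "secondary outcomes were ‘The line bisection test’, ‘Modified Taylor Complex Figure’, ‘NIHSS’ and neuroimaging assessments". Study design repeats the test as a secondary outcome. On timing, the Abstract says: "Assessments will be performed before the intervention, at the end of the intervention, and followed up at 6 and 14 weeks". The behavioural analysis section plans to analyse the measures in three groups at four time points.

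The Assessment section hands the detail to the table: "The patient’s assessment arrangements are shown in Table 1". In Table 1 the row labelled "The Line bisection test" names Assessor B, and all its visit cells are empty.

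The section on the test describes the task, "Three horizontal, 8-inch black lines, 1-mm thick, will be presented to each patient in a staircase fashion across the page", and one expected error: "It is expected that patients with left neglect will choose a midpoint to the right of true center". It does not say whether the score is signed, absolute or referenced to the lesion, or how three marks become one value.

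Eligibility restricts handedness but not lesion side, and stimulation follows the lesion: "The affected side of the brain will receive dual-target transcranial magnetic stimulation". Between-group comparison is by one-way ANOVA for measures that pass a normality test and by Kruskal-Wallis otherwise. No lesion-side term is mentioned.

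**The concern.** Table 1 is the only place where visits are assigned outcome by outcome. Staff working from it would have no visit at which to give the line bisection test, although the text counts it as a secondary outcome. It is one of two dedicated visuospatial measures in a trial whose rationale is visuomotor integration, and a missed baseline cannot be recovered.

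The second matter is how the result would be scored. The one direction described belongs to left neglect. Patients with lesions on the other side would be expected, if they have a lateral bias at all, to err the other way. A raw left-right deviation averaged over both kinds of patient would set these errors against each other. With no score fixed in advance, the choice between signed and absolute deviation could also be made after the data are seen.

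**Working it through.** **Step 1. Count the marks in Table 1.** The assessment columns used are week 0, end of week 2, end of week 6 and the last column.

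| Outcome | Visits marked |
|---|---|
| FMA-UE | 4 |
| Line bisection | 0 |
| MTCF | 4 |
| NIHSS | 4 |
| fMRI | 4 |
| DTI | 4 |

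Six outcomes at four visits would need 6 × 4 = 24 marks. The table has 5 × 4 = 20. The four absent marks all fall in one row.

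**Step 2. Could the marks have been lost in reading the PDF?** The row kept its label and its assessor. The rows directly above (FMA-UE) and below (MTCF) kept their marks in the same columns. Loss confined to this row is possible but less likely than an omission in the table.

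**Step 3. Does this touch the sample size?** The article gives no figure for line bisection. Its only calculation uses means 8.11, 6.87 and 17.62, SD 8.83, α = 0.025 and power 0.90.
- Grand mean: 32.60/3 = 10.867.
- Sum of squared deviations: 7.60 + 15.97 + 45.61 = 69.18.
- Noncentrality at 18 per group: 18 × 69.18/8.83² = 15.97.
- The noncentral F power is 0.902, and 18 is the smallest group size that reaches 0.90. The total is 54, as stated.
- With 20% dropout: 18/0.8 = 22.5, so 23 per group and 69 in all, as stated.

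Nothing about line bisection enters this calculation, so it stands.

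**Step 4. Dilution if the score were a raw left-right deviation.** The documents give neither the lesion mix nor the size of the error, so what follows is assumed. Let p be the share of right-hemisphere lesions. These patients err by +d (rightward), and left-hemisphere patients err by −r·d.
- Raw pooled mean: d[p − (1 − p)r].
- Mean referenced to the lesioned hemisphere: d[p + (1 − p)r].
- If treatment removes the same fraction of the bias on both sides, its effect is diluted in the same ratio.

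| p | r | Raw | Lesion-referenced | Share kept |
|---|---|---|---|---|
| 0.5 | 1 | 0 | d | 0% |
| 0.6 | 1 | 0.2d | d | 20% |
| 0.7 | 1 | 0.4d | d | 40% |
| 0.5 | 0.5 | 0.25d | 0.75d | 33% |
| 0.5 | 0.25 | 0.375d | 0.625d | 60% |
| 0.5 | 0 | 0.5d | 0.5d | 100% |

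At p = 0.4 and r = 1 the raw mean is −0.2d: again 20% in size, with the sign reversed. Complete cancellation needs both an equal mix and mirror-equal errors. If only right-hemisphere patients are biased (r = 0), the sign convention costs nothing in the mean.

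**The case against.** A reader might infer that the trial will collect no line bisection data. The documents do not support that. The test is a named secondary outcome, an assessor is assigned to it, and the text gives four assessment times in general and analysis at four time points. Read as a whole, the article plans to collect it. What stands is a conflict between table and text, probably an omitted row of marks. A fault in reading the table cannot be excluded.

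A reader might also infer that pooled signed errors will cancel and produce a null result. That goes too far as well. The article never says the score is signed. Under absolute or lesion-referenced scoring nothing cancels. Neglect is not an entry criterion, so the article does not show that enrolled patients have a lateral bias to dilute. ANOVA applies only to measures that pass the normality test. A rank test on a raw signed score would also mix directions, but the formula for the mean does not carry over to it.

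Finally, a journal article condenses, and the scoring rule may stand in the full protocol; MTCF has no scoring rule here either. So a missing rule is not in itself the defect. What remains is narrower: the only direction the article gives fits one lesion side, in a trial open to both.

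**Conclusion.** The schedule conflict holds. Table 1 marks 0 of 4 visits for line bisection and 4 of 4 for every other outcome, against a text that names the test as an outcome and implies four assessments. This rests on the table as printed being as it was read.

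The scoring point holds only conditionally. If the score is a raw left-right deviation pooled over lesion sides, the share of the bias or effect that is kept runs from 0% (equal mix, mirror-equal errors) to 100% (errors on one side only), depending on values the article does not give. It is a reason to fix the score in advance, not a prediction of a null result.

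Both matters are minor. The primary outcome and the sample size do not change.

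**What to change.** In Table 1, mark the line bisection test at the same four visits as MTCF. The last column there is headed 10 weeks, while the text gives the final follow-up as 14 weeks; that label needs reconciling for all outcomes, but it is a separate matter.

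Add one sentence on scoring, for example: *For each line the deviation of the mark from true centre is recorded, signed relative to the lesioned hemisphere (positive = toward the lesioned hemisphere); the score is the mean over the three lines, and groups are compared with adjustment for the baseline score.* Referring to the hemisphere, not to the affected side, avoids confusion with the paretic side of the body, which would reverse the sign. If the full protocol already defines the score, check it against this and cite it.

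The cost is four table marks and one sentence, settled before unblinding. No extra procedure is needed, because the affected hemisphere must be known to deliver the stimulation.
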